## Study procedures

All the patients will undergo a non – invasive, transabdominal fECG during regular outpatient clinic appointments, performed by one of the researchers. This test has a very low grade of discomfort for the patient. The conducted fECG will be stored on an external hard drive, the data will be analyzed by researchers of the Technical University. The last two investigators will look at the fECG and will determine the segment intervals, the heart axis and the amplitudes. After the analysis, we will be able to enter the data in SPSS to conduct normal values and ranges with 95% confidence intervals. The patients will not be notified of any abnormal findings on the fECG, because this is a pilot study. We do not know for certain that any abnormalities we find are actually real abnormalities. This is something we want to investigate.

In the cross-sectional study, we want to know if the fetuses we included are born healthy. Therefore, we will evaluate this with a simple questionnaire which we will send four to six weeks postpartum. We believe this questionnaire will be sufficient to evaluate if any severe CHD was present at birth, because a severe CHD has hemodynamic consequences which present early in neonatal life. Besides, we have permission to withdraw patient information at the postnatal clinic or attending pediatrician. If the neonate has a congenital heart disease missed by the SEO, we will exclude the patient from the cross-sectional study and will evaluate the data of the fECG in the case-cohort study. If the participants do not return the questionnaire, they will be excluded from further analyses.

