# 3. STUDY DESIGN

Both the cross-sectional and case-cohort study are prospective in nature. In the future, a longitudinal cross-sectional study can be performed based upon this study.

The cross-sectional study will take place in the MMC, Veldhoven, the Netherlands and Diagnostic center Eindhoven, the Netherlands. All the patients who visit the outpatient clinic for the first time will receive information about the research. Patients who visit the Diagnostic center Eindhoven will receive information about the research via their appointment confirmation e-mail. Measurements will be performed before or after the SEO or GUO-1 after written informed consent; patients do not have to come to the hospital or the diagnostic center for an extra visit.

The case-cohort study will take place in the MMC Veldhoven, and the medical centers Radboud MC Nijmegen, Academic Medical Center Amsterdam, and Maastricht UMC the Netherlands. Whenever a patient is diagnosed with a fetal severe CHD in any of these centers by using the SEO and the GUO, they will inform the patient about our research and contact us after informed consent. We will perform a fECG during routine follow up visits in those centers. For more information on recruiting the patients, see chapter 9, paragraph 9.2 “Recruitment and consent”.

In the cross-sectional study, 200 pregnant women will be included. With this amount of patients, we can determine with the wanted accuracy what the normal values and 95% CI of a healthy fetus are^9, 10^. If any of these fetuses is diagnosed with a CHD, they will automatically be evaluated in the case-cohort study.

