In the case-cohort study, we will include pregnant women carrying fetuses with a form of severe CHD, preferably with the same CHD. A severe CHD is defined as possibly life threatening and/or needing intervention or surgery in the first year of life. For now, we believe that of every CHD, we need 10 patients to determine the difference between the normal values and the segment intervals of the fetuses with this severe CHD. The overall incidence of CHD is 4 to 9 per 1000 living newborns^4^. Because of this low incidence, it would take years to include more than 10 fetuses per form of severe CHD. Because of this reason, plus the fact this concerns a pilot study, we chose to include 10 fetuses per form of severe CHD. Because of this low incidence, collaboration with more than one center is needed. We believe that we will be able to collect data of the fECG of 10 fetuses with the support of the other centers.

The fECG signals are stored and digitized by a program named the NEMO system^1^. More details can be found in chapter 4.

With the collected data, we will perform several sub-analyses. We will calculate the normal values and ranges of the amplitudes (P, QRS, T), and the segment intervals with 95% confidence intervals. We will also evaluate the heart axis of the fetus. This data will be compared with the collected data of the fetuses with CHD. The patients will not be notified of any abnormal findings on the fECG, because this contains a pilot study and any findings on the fECG are still being evaluated. Therefore, this research does not have any consequences for the standard care plan of the patients and their fetuses.

If any of the fECG turns out to be abnormal, it will not influence the treatment of the fetus. The main reason for the last fact is that we do not know if the findings we think are abnormal are actually abnormal. This is one of the aspects we would like to investigate.

In the future, a longitudinal research is needed to determine the sensitivity and specificity of fECG.

Approximately 10 weeks postpartum, the patients from the cross-sectional study will receive a questionnaire about their delivery and their newborn and patient information can be withdrawn from the postnatal clinic or the attending pediatrician. If the participants do not return the questionnaire, they will be excluded from further analyses.

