## Sample size calculation

This will be the first study to investigate the clinical contribution of fECG for the diagnosis of severe CHD. We believe that a total of 200 patients will be enough to evaluate the normal range or value of the different segment intervals and amplitudes of the fECG, as described in the literature by Douglas G. Altman^10^. For the case-cohort study, we believe that a total of 10 patients per severe CHD will be enough for the evaluation and the comparison of the fECG of a healthy fetus and the fECG of a fetus with known severe CHD. No sample size calculation was used in the estimation of the size of the population for the case-cohort study, since this is a pilot study.

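### A cross-sectional recording is dropped when the questionnaire is not returned, even if the newborn's records could establish the outcome, and the questionnaire has two conflicting dates

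*Protocol*

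**What the plan says.** The primary objective is the normal range of fetal ECG (fECG) values in healthy fetuses. On the size of that group, section 3 says "In the cross-sectional study, 200 pregnant women will be included" and adds that with this number "we can determine with the wanted accuracy what the normal values and 95% CI of a healthy fetus are". Section 4.4 gives the basis: "We believe that a total of 200 patients will be enough to evaluate the normal range or value", with a textbook reference. Neither section mentions losses or replacement.

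Whether a fetus was in fact healthy is checked after birth. Section 8 uses the questionnaire to decide, fetus by fetus, whether the recording can be used. On non-return, sections 3 and 6.3 carry the same sentence: "If the participants do not return the questionnaire, they will be excluded from further analyses".

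Both sections also name another source for the same fact. Section 6.3 says: "Besides, we have permission to withdraw patient information at the postnatal clinic or attending pediatrician". Section 3 says in similar terms that this information can be obtained, directly before the exclusion rule.

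The timing differs between the two sections. Section 3 has: "Approximately 10 weeks postpartum, the patients from the cross-sectional study will receive a questionnaire". Section 6.3 has: "a simple questionnaire which we will send four to six weeks postpartum". Both are current text.

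**The concern.** The rule makes a returned form the condition for analysis, when what matters is knowing the newborn's cardiac status. Where the form is missing but the records would answer the question, a usable recording is thrown away. Nothing in either section makes exclusion wait until the records have also failed.

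Three things are at stake:

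- **Precision.** The 200 are women included, not recordings analysed, so each unreturned form takes the analysed number below the one the protocol relies on.
- **Composition.** The reference sample becomes a sample of responders. Response may depend on how the newborn fared, or on features of the mother.
- **Missed cases.** Sections 3 and 6.3 send a congenital heart defect (CHD) found in this group to the case-cohort part. If the mother does not reply, such a case drops out of both parts.

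The date conflict adds to this. The step that defines the primary analysis set has no single time point, so staff following different sections would ascertain outcome at different ages.

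**Working it through.** **The plan's own figure.** The 200 cannot be reproduced. Sections 3 and 4.4 give no standard deviation, target interval width or loss rate. The figures below show what the rule costs relative to 200 analysed, not whether a stated target is missed.

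**Precision.** Assume approximately normal values and a reference limit at mean ± 1.96 SD. In SD units:

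- half-width of the 95% CI of a reference limit = 1.96 × √(1/n + 1.96²/(2n))
- half-width of the 95% CI of the mean = 1.96/√n
- relative widening of either = √(200/n) − 1
- women to enrol to keep 200 under the present rule = 200/(return rate), rounded up

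For n = 200: 1.96 × √(0.005 + 3.8416/400) = 1.96 × 0.1208 = 0.237. For n = 120: 1.96 × √(0.00833 + 3.8416/240) = 1.96 × 0.1560 = 0.306.

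The protocol gives no return rate, so the first column is an assumption.

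| Return | Analysed n | Limit, half-width (SD) | Mean, half-width (SD) | Widening | Enrolment to keep 200 |
|---|---|---|---|---|---|
| 100% | 200 | 0.237 | 0.139 | 0 | 200 |
| 90% | 180 | 0.250 | 0.146 | 5% | 223 |
| 80% | 160 | 0.265 | 0.155 | 12% | 250 |
| 70% | 140 | 0.283 | 0.166 | 20% | 286 |
| 60% | 120 | 0.306 | 0.179 | 29% | 334 |

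If records settled the status of every non-responder, the first row would apply, less any CHD found.

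**Missed CHD lost through the rule.** Inputs: incidences per 1000 live births from Appendix I, and SEO detection of 25 to 60% from section 1, so 40 to 75% missed.

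1. Listed forms: 0.59 + 0.31 + 0.75 + 0.25 + 0.22 + 0.49 = 2.61 per 1000.
2. Expected in 200: 200 × 0.00261 = 0.52.
3. Missed by the SEO: 0.52 × 0.40 = 0.21 to 0.52 × 0.75 = 0.39.
4. Lost through non-return, if response is unrelated to outcome: 0.21 × 0.10 = 0.02 to 0.39 × 0.40 = 0.16.

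Step 3 counts every missed case among the 200; only step 4 counts those this rule would remove. The total is approximate in both directions. Atrioventricular septal defect is an included form with no row in Appendix I. The pulmonary row (0.75) combines stenosis with atresia, while section 4.2 lists only atresia. Without that row the sum is 1.86 per 1000. Then 200 × 0.00186 = 0.37, of which 0.15 to 0.28 are missed and about 0.015 to 0.11 lost.

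**Dates.** About 10 weeks (section 3) and four to six weeks (section 6.3) do not overlap. No other passage decides between them.

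**The case against.** The strongest defence is that non-responders are of unverified status, and leaving an unverified fetus out of a normal range is conservative. This stands where no source can settle the outcome. It does not cover a recording whose outcome is available from a source the protocol says it may use. One could also suppose that the records are meant to be consulted first, but neither section says so, and the exclusion sentence has no qualifier.

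A second defence is that selection may do little harm. If the mothers who do not reply are mainly those of sick or deceased newborns, many of the fetuses lost do not belong in a healthy reference group. The protocol offers no evidence linking reply to fECG values at 18 to 24 weeks. This stands: selection is a risk whose direction and size are unknown.

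Third, the loss of precision is modest at 10 to 20% non-return, and the accuracy wanted is never quantified, so no target is shown to be missed. This also stands.

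A reader might further infer that either date is too early and leaves late-presenting CHD in the healthy group, because the definition of severe CHD in section 3 includes defects "needing intervention or surgery in the first year of life". The document does not support that. Age at intervention is not age at presentation, the same definition also covers life-threatening defects, and section 6.3 argues that severe CHD shows itself early after birth. Nothing in the protocol contradicts that argument.

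**Conclusion.** The point holds as a defect in how the analysis set is defined. The exclusion is unconditional in two sections that each name a second source, and it reduces the reference sample below the 200 included, with no allowance.

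Its size depends on a return rate the protocol does not give. Between an assumed 90% and 60% return, a reference limit's interval is 5% to 29% wider, with 180 to 120 recordings left.

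Two stronger readings are tempting. One is that the rule discards fetuses known to be healthy; their status is simply unconfirmed. The other is that it is likely to cost the study an informative missed case. The expected number lost is about 0.02 to 0.16 if response is unrelated to outcome. Even if every missed case fell among non-responders, it would stay below 0.4 on the listed incidences.

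The date conflict is certain from the text. The matter should be corrected before analysis, but it does not by itself invalidate the primary objective.

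**What to change.** In sections 3 and 6.3, replace the exclusion sentence with one rule. When the questionnaire is not returned, neonatal cardiac status is taken from the postnatal clinic or pediatrician under the permission already claimed. The recording is excluded only if neither source establishes status. Report the number excluded for this reason.

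State one questionnaire date in both sections. The protocol gives no ground for preferring either date, so the sponsor must reconcile them.

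The cost is a short amendment, a record look-up for each non-responder and a slightly later data lock. The consent form is not part of the text reviewed, so the sponsor should confirm that its scope covers this look-up for women who do not reply. Keeping the present rule and enrolling more women to preserve 200 would take 223 to 334 participants over the same assumed range, which is the more expensive route.

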## Withdrawal of individual subjects

If subjects do not want to proceed with the measurement, they can step out at any moment. There are no follow – up moments, which makes it easier for the patients to join the research.

# 7. SAFETY REPORTING

## Section 10 WMO event

In accordance to section 10, subsection 1, of the WMO, the investigator will inform the subjects and the reviewing accredited METC if anything occurs, on the basis of which it appears that the disadvantages of participation may be significantly greater than was foreseen in the research proposal. The study will be suspended pending further review by the accredited METC, except insofar as suspension would jeopardize the subjects’ health. The investigator will take care that all subjects are kept informed.

## 7.2 AEs and SAEs

### 7.2.1. Adverse events (AEs)

## We don’t expect any adverse events during the study, however when applying the electrodes on the skin, an allergic reaction can exist. This is rare.

### 7.2.2. Serious adverse events (SAEs)

A serious adverse event is any untoward medical occurrence or effect that:

- results in death;
- is life threatening (at the time of the event);
- requires hospitalization or prolongation of existing inpatients’

hospitalization;

- results in persistent or significant disability or incapacity;
- is a congenital anomaly or birth defect;

Any other important medical event that may not result in death, be life threatening, or require hospitalization, may be considered a serious adverse experience when, based upon appropriate medical judgment, the event may jeopardize the subject or may require an intervention to prevent one of the outcomes listed above.

We do not expect SAEs during the study due to the non-invasive technique we use, but if any SAE occurs we will report them and, if necessary, the patient will be followed by a medical doctor.

## Reporting adverse events

If an allergic reaction exists, we will report this as an adverse event after the study has been closed. Other (unexpected) SAEs, will be reported directly and these patients will be followed by a medical doctor, if this is necessary. The sponsor will report the unexpected SAEs through the web portal *ToetsingOnline* to the accredited METC that approved the protocol, within 15 days after the sponsor has first knowledge of the serious adverse reactions. SAEs that result in death or are life threatening should be reported expedited. The expedited reporting will occur not later than 7 days after the responsible investigator has first knowledge of the adverse reaction. This is for a preliminary report with another 8 days for completion of the report

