# 1. INTRODUCTION AND RATIONALE

During pregnancy, multiple ultrasound examinations are performed to assess the fetal condition. This is executed, amongst others, during or around week 20 of gestational age and is called the fetal anomaly ultrasound (SEO in Dutch). With this technique, all kind of possible congenital anomalies can be detected, including CHD. However, a false negative diagnosis occurs frequently and the SEO only detects 25 to 60 per cent of the patients with CHD^1, 2^. That makes CHD the most common structural fetal abnormality of which a significant part is missed during the prenatal life.

CHD can be divided into cyanotic and non-cyanotic. An example of cyanotic CHD is Fallot’s tetralogy or a transposition of the great vessels. An example of the non-cyanotic form is an aortic stenosis, atrial septum defect or an aortic coarctation. The incidence of CHD is estimated to be 4 to 9 per 1000 live born^3^. In the Netherlands, the overall incidence of anomalies of the vascular system is estimated at 6,6 per 1000 live births^4^. The incidence of severe CHD (read, of hemodynamic importance) is low (see appendix I. page 27).

The survival for patients with CHD is low, 21 percent^2, 3^, and the prognosis is negatively influenced by the presence of heart failure, aneuploidy or extracardial malformations. There are several studies which show a correlation between an abnormal heartbeat of the fetus and the diagnosis CHD. These patterns can be diagnosed with ultrasound (including the Doppler technique), which is the current method for prenatal screening of CHD. If a CHD is suspected or seen on the SEO, the patient will receive a more intensive ultrasound, named the GUO (geavanceerd ultrageluids onderzoek) in Dutch. If the CHD is confirmed with the GUO, the fetus has a high certainty of having a CHD. In 2003, the Dutch magazine of medicine (in Dutch: Nederlands tijdschrift voor geneeskunde) reported a sensitivity of 94,7%, a specificity of 98,8%, a positive prognostic value of 95,3% and a negative prognostic value of 98,6%^5^

However, these routine controls with ultrasound can only diagnose about 25 to 60 per cent of the large heart defects^1, 2^. The disadvantage of Doppler ultrasound is that there can be false – negatives. Plus the fact that Doppler can’t detect beat – to – beat heart rate, which causes several heart abnormalities to be missed.

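### Section 7.3 routes allergic reactions by type, not by seriousness, and 7.2.2 does not say how CHD, the case entry criterion, is handled as a possible SAE

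*Protocol*

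**What the plan says.** Section 7.2.1 of the protocol names one foreseeable adverse event, an allergic reaction to the electrodes, and calls it rare. Section 7.3 then gives the reporting rules:

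- For allergic reactions: "If an allergic reaction exists, we will report this as an adverse event after the study has been closed".
- For the rest: "Other (unexpected) SAEs, will be reported directly and these patients will be followed by a medical doctor, if this is necessary".
- Unexpected SAEs go to the METC within 15 days, counted from the sponsor's knowledge of serious adverse reactions.
- Fatal or life-threatening SAEs are expedited within 7 days, counted from the responsible investigator's knowledge of the adverse reaction, with 8 more days to complete the report.

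Section 7.2.2 opens its definition with "A serious adverse event is any untoward medical occurrence or effect that" and lists, among other criteria, "results in death", hospitalization and "is a congenital anomaly or birth defect". It promises that any SAE will be reported, without a time limit, and adds "We do not expect SAEs during the study due to the non-invasive technique we use".

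The case-cohort part enrols only women whose fetus has a known severe CHD (section 4.2). In the cross-sectional part, section 6.3 looks for CHD missed by the anomaly scan, by questionnaire and from medical records after birth. A fetus found to have one moves to the case-cohort analysis.

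**The concern.** Two things make the rules hard to follow.

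First, the reporting route for the one procedure-related harm that the protocol names depends on what the event is, not on how serious it is. The deferral sentence has no seriousness qualifier, and the direct-reporting sentence begins by setting allergic reactions aside. A serious reaction to the measurement could therefore follow the slowest route.

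Second, the SAE criteria are a general list, not adapted to a cohort selected because the fetus has a birth defect. The protocol does not say whether fetal and neonatal events count, over what period, or whether the qualifying CHD is a baseline condition. Because 7.3 also alternates between events and reactions, one reader would report a fetal death from the heart defect and another would not. Cases come from several centres (sections 3 and 9.2), so both readings could be applied in the same study.

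**Working it through.** **1. Route of an allergic reaction, by seriousness**

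| Reaction | Deferral sentence (7.3) | Direct and 15-day sentences (7.3) | Expedited sentence (7.3) | Result |
| --- | --- | --- | --- | --- |
| Non-serious | applies | do not apply | does not apply | consistent: after closure |
| Serious, not life-threatening (e.g. hospitalization) | applies, no qualifier | direct route covers only other SAEs; both sentences cover only unexpected ones, and this type is foreseen in 7.2.1 | does not apply | an SAE under 7.2.2, deferred by 7.3 |
| Fatal or life-threatening | applies, no qualifier | as above | applies, with no exception for allergic reactions | two sentences conflict |

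Section 10.4 asks for serious events in the annual report, which does not fit a deferral to closure for the second and third rows either.

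**2. Terms and clocks**

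- 15-day rule: applies to unexpected SAEs; the clock starts when the sponsor learns of serious adverse reactions.
- 7-day rule: applies to fatal or life-threatening SAEs; the clock starts when the investigator learns of the adverse reaction.

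Each rule names an event as its trigger and a reaction as its clock start, and the two start with different parties. An SAE need not be caused by the measurement; a reaction implies that it was.

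**3. SAE list against the case population**

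The plan's figure is 60 cases (section 4.1): 6 forms x 10 = 60, reproduced. The Summary and section 4.2 list seven conditions, because pulmonary atresia is named separately; that would give 7 x 10 = 70. On the bare wording of the birth-defect criterion, 60 of 60 cases meet it (70 of 70 with seven forms).

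**4. CHD first found after birth in the cross-sectional cohort**

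Inputs: 200 fetuses (section 4.1); 6.6 per 1000 live births, the Dutch figure in section 1, with a general range of 4 to 9; detection by the anomaly scan of 25% to 60% (section 1). Assumption: these general figures apply to this cohort.

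Expected missed = 200 x incidence x (1 - detection). P(at least one) = 1 - (1 - incidence x (1 - detection))^200.

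- 6.6 per 1000, detection 60%: 200 x 0.0066 x 0.40 = 0.53; P = 41%.
- 6.6 per 1000, detection 25%: 200 x 0.0066 x 0.75 = 0.99; P = 63%.
- Extremes: 200 x 0.004 x 0.40 = 0.32 (P = 27%) and 200 x 0.009 x 0.75 = 1.35 (P = 74%).

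The figures cover all CHD, not only severe forms. Such an event is about as likely as not. Section 6.3 foresees it but says only which analysis it joins, not whether it is an SAE.

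**5. Exposure to the electrodes**

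200 + 60 = 260 women. The protocol gives no rate for allergic reactions. Assuming 0.1% to 1% for any severity, 260 x 0.001 = 0.26 to 260 x 0.01 = 2.6 reactions; serious ones would be a subset.

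**The case against.** The best defence is that the deferral sentence speaks of a reaction reported as an adverse event, so it was probably written with mild skin irritation in mind. Section 7.2.2 promises to report any SAE, and the expedited sentence makes no exception for allergic reactions. A reader might infer that even a life-threatening reaction waits for closure; the text does not support that, because the expedited sentence covers it. The open gap is the serious but not life-threatening reaction, plus a conflict of wording above that grade.

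The qualifying CHD precedes enrolment, so it is naturally read as baseline and not as an untoward occurrence. The statement that SAEs are not expected gives the technique as its reason; it does not call CHD or its course unexpected. Both points stand. They do not settle a fetal or neonatal death after enrolment, or a CHD first found after birth.

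A reader might also combine "The survival for patients with CHD is low, 21 percent" with 60 cases, 60 x (1 - 0.21) = 47.4, and infer that most of these deaths would be expedited SAEs. The documents do not support this. The 21% has no time horizon and refers to CHD in general. The postnatal questionnaire goes to the cross-sectional cohort only, and section 6.4 has no follow-up moments. The number of deaths inside the study cannot be computed.

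Nor does the deferral disable section 7.1 ("The study will be suspended pending further review by the accredited METC"). The investigator can trigger it without any report under 7.3, and the principal investigator asks for weekly updates (10.2). The annual report has room for other problems as well as serious events. The protocol states no recruitment duration, so how long a deferral would last is unknown.

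Finally, the researchers perform the recordings themselves (6.3) and safety is not an endpoint, so differences between centres would not affect a planned analysis. That stands, and it keeps the severity low.

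**Conclusion.** The point holds as a low-severity defect of wording with a safety aspect. Section 7.3 defers a serious but not life-threatening allergic reaction that 7.2.2 defines as an SAE, and it contradicts itself for fatal or life-threatening ones. It mixes events with reactions and starts its two clocks with different parties. Section 7.2.2 leaves open whose events count, over what window, and how the qualifying CHD, its known course and a newly found CHD are treated.

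In size: up to 260 women are exposed to a reaction that the protocol calls rare; all 60 cases meet a criterion, but only on a literal reading; and 0.53 to 0.99 missed CHDs are expected in the cross-sectional cohort (0.32 to 1.35 over the wider incidence range), if general incidence and scan detection apply. No endpoint, sample size or analysis changes.

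**What to change.** - **Section 7.3, route.** Reconcile the sentences: limit the deferral to non-serious allergic reactions and delete the word Other from the next sentence. Deleting that word alone would leave the deferral in place. State also that a serious allergic reaction is not excluded by the word unexpected merely because skin reactions are foreseen. Seriousness then sets the route for every event.
- **Section 7.3, terms.** Use one term, SAE, and one clock start throughout.
- **Section 7.2.2.** State whether maternal, fetal and neonatal events count, and over what window. State that pre-existing CHD and its known course are not reported expedited unless judged related to the measurement. State how a CHD first found after birth in the cross-sectional cohort is handled.
- **Section 10.4.** List non-serious skin reactions under other problems in the annual report, so that the METC sees them while the study runs.

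The cost is a wording amendment notified to the METC and one added line in a report already due. No data collection or analysis changes, unless the stated window adds postnatal outcomes of cases.
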